#### Action plan

3.6.2

Participants will receive a six-week supply of e-cigarettes, distributed weekly, according to their flavor assignment. Before beginning the switch phase, participants will meet with a research staff member to receive instructions on how and when to use the e-cigarette and to develop an action plan for switching [8,14]. The 30-min action plan will include preparing for switch day, managing smoking triggers, and garnering support for behavior change. Studies have shown that brief preparation for switching from combustible to e-cigarettes is associated with higher smoking abstinence rates at 8 weeks and greater reductions in harmful chemical exposure than participants not receiving instructions [8,14], even among smokers uninterested in quitting smoking immediately [8]. As such, the action plan enables all participants to begin with the same level of preparation while maximizing external validity.

#### Switch period (Weeks 2-7, days 8-49)

3.6.3

Participants will leave the laboratory assessment on day 7 with instructions for e-cigarette use, a device, a charger, and a 7-day supply of pods matching their group assignment. The 7-day supply (days 8–14) will be based on baseline cigarettes smoked per day (1 pod per pack smoked), with an extra pod in case a participant cannot attend a scheduled appointment [8,14]. Participants assigned to the fruit flavor can choose blueberry and watermelon. Those assigned to tobacco or menthol will receive their respective flavors. As in previous studies involving tobacco product switching [32,35,41], participants will be instructed to switch completely from combustible cigarettes to e-cigarettes (Day 8). Complete switching instructions lead to larger changes in smoking behavior than ad libitum use [8] or gradual reduction [42].

A written instruction card for collecting and storing used pods will be reviewed with each participant. Participants will receive seven date-stamped zipped baggies to collect used pods daily [32,33]. They will return to the Center on days 14, 21, 28, 35, 42, and 49 to have their CO measured, return their used pods, and receive their next seven-day supply of pods and zipped baggies (no pods or baggies on day 49). Participants will earn a $20 incentive at each visit. They will collect all used pods through day 49. Although the expectation is that participants will only use e-cigarettes, it's realistic to expect some will also smoke combustible cigarettes. We will ask participants to collect their spent cigarette filters if they smoke and place them in a date-stamped baggie. Participants will receive a $10/day incentive for collecting used pods and spent cigarette filters.

### Follow-up (Weeks 8-26)

3.7

The switch phase will conclude at the end of week 7. Participants will then receive information on where and how to buy common e-cigarette brands, with attention to nicotine content [43]. Details on open and closed e-liquid systems, including disposables and potential purchase locations, will also be provided [44]. While non-disposable menthol and tobacco-flavored pod-style e-cigarettes are widely available, fruit-flavored pod-style e-cigarettes are less accessible. Up to 39% of brick-and-mortar stores continue to sell them, and online stores remain a possible source [45]. Disposable fruit-flavored pod-style e-cigarettes are easily found in vape shops throughout the city area, as are open e-cigarette systems that allow adding fruit-flavored e-liquid.

Participants will complete an in-person follow-up at 26 weeks. This follow-up will allow an assessment of cigarette smoking behavior, ongoing e-cigarette use [14], and the characteristics of e-cigarette use (such as device type, flavor, quantity of use, and nicotine content). This will enable us to observe short-term and long-term sustained switching, delayed switching, shifts in dual use, and the return to exclusive smoking [46] as participants navigate the current and evolving tobacco marketplace.

### Assessments

3.8

Table 1 summarizes the measured variables and their measurement time points. Covariates will include demographics, smoking history, e-cigarette use history, marijuana use, nicotine dependence as measured by the Fagerstrom Test for Nicotine Dependence [47], the modified Penn State Dependence Scale [48], carbon monoxide measured with iCO quit (Bedfont Scientific), depression symptoms measured with the 20-item Center for Epidemiological Studies - Depression scale [[49], [50], [51]], and anxiety measured with the Generalized Anxiety Disorder-7 [52,53].

**Table 1 tbl1:** Schedule of study measures.

Measures	Laboratory Visits				
	Baseline	Day 6	Day 7	Weeks 2-7	Week 26
**Baseline Covariates**					
Demographics	X				
Smoking History	X				
E-cigarette History	X				
Nicotine Dependence	X			X	X
Cigarettes per day (days 1-5)	X				
Depression & Anxiety	X				
CO	X	X	X	XXXXXX	X
**Predictor Variables**					
Craving Relief		X			
Withdrawal Relief		X			
Negative Affect		X			
ECIG pods per day				XXXXXX	X
**Mediating Variables**					
Subjective Reward		X			
Relative Reinforcing Value of Flavoring			X		
Positive Affect		X			
**Outcome Variable**					
Cigarettes per day				XXXXXX	X

Predictor variables will include craving, measured by the 10-item Brief Questionnaire of Smoking Urges [54,55]; withdrawal symptoms, assessed with the Minnesota Nicotine Withdrawal Scale [56,57]; and negative affect, evaluated using the Positive and Negative Affect Schedule [[58], [59], [60]]. Additionally, e-cigarette use will be recorded by counting the daily e-cigarette pods returned over each of the 42 days of the switch period (days 8–49) [32,35,61]. The total number of pods used during the switch phase will be determined by summing fully and partially used pods. Partially used pods will be weighed and converted into a fraction of a pod used [61].

Mediating variables include the subjective rewarding value of e-cigarette flavor, measured with the Satisfaction Subscale of the modified Cigarette Evaluation Questionnaire adapted for e-cigarette use [23,[62], [63], [64]]; positive affect measured with the Positive and Negative Affect Schedule [[58], [59], [60]], and the relative reinforcing value of flavor measured with a validated computer-based choice paradigm, which evaluates the preference for flavored e-cigarette puffs versus cigarette puffs [37,65].

The primary outcome is the longitudinal daily count of cigarettes from baseline to the end of the e-cigarette switch phase. Daily cigarette consumption will be determined by counting the daily spent cigarette filters returned for each of the 42 days (days 8 – 49) [32,35]. Cigarette smoking behavior at the 26-week follow-up will serve as a secondary endpoint. Average CPD at the 26-week follow-up will be measured via a valid and reliable TLFB procedure [66]. A CO value < 5 ppm will verify combustible cigarette abstinence (complete switching) at these time points.

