**Fig. 1 fig1:**
[figure not shown]
Overview of study design.

Participants will then receive instructions and an action plan to switch to e-cigarettes for the following 6 weeks (weeks 2-7). Participants will collect their used cigarette filters and their used e-cigarette pods daily to assess consumption of cigarettes per day (CPD) and pods per day (PPD). The primary outcome will be the longitudinal daily count of cigarettes from baseline to the end of the 6-week e-cigarette switch phase. A secondary endpoint will be cigarettes per day from week 8 to week 26, measured by timeline-follow-back (TLFB). Complete switching will be verified with a carbon monoxide (CO) value < 5 ppm. Secondary outcomes include subjective reward, relative reinforcing value, and positive affect. The protocol was approved by the University of Pennsylvania's Institutional Review Board (854051) and participants provided written informed consent.

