### Baseline smoking assessment (Week 1, days 1-5)

3.4

Participants will be instructed to smoke as usual on days 1-5. They will receive five date-stamped zipped baggies [32,33]. A written instruction card for collecting and storing spent cigarette filters will be reviewed with each participant. Participants will collect all spent filters through day five and receive a monetary incentive ($35) to return the baggies [32,33]. Participants will return used cigarette filters in the date-stamped zipped baggies at the day 6 laboratory visit. Participants will be randomized to fruit, tobacco, or menthol-flavored e-cigarettes in an unblinded manner, with the computerized allocation sequence generated by the biostatistician and accessible only to the data manager. Randomization will be stratified by sex, nicotine dependence, depression/anxiety, and menthol cigarette status.

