#### Sample size

3.10.1

For Aim 1, hypotheses will be tested with 80% power using 5% two-sided alpha Bonferroni corrected to 2.5% for two group comparisons. The primary outcome is the longitudinal daily cigarette count from baseline (days 1-5) to the end of the e-cigarette switch phase (day 49), with week 26 as a secondary endpoint. We based the power on data from prior switching studies. A sample of 210 (70 per group) will allow us to detect an overall standardized slope of 0.19. To account for a ∼15% attrition rate [67], we will enroll ∼ 240 participants to have 210 who complete the 26-week follow-up. We expect the initial and sustained switch for participants randomized to fruit-flavoring to be greater than for participants randomized to tobacco or menthol flavoring. A sample of 70 per group enables us to detect a difference of ∼3.73 cigarettes per day (CPD). We will also be able to detect a difference in slopes of 0.13 (CPD per day change).

For Aim 2, a sample of 70 per group will allow us to detect a between-group effect size of 0.5. For the relative reinforcing value of flavored e-cigarettes (RRVF), this means we can detect a difference in breakpoint of 2.0. Positive affect will be assessed as a difference score with a standard deviation of approximately 7.0, yielding 80% power to detect a difference of approximately 3.7. Subjective reward has a standard deviation of 1.3, which allows us to detect a 0.68 difference. In turn, the continuous measures of RRVF, positive affect, and subjective reward will be used to predict changes in mean cigarette counts from baseline to the end of the switch phase and from baseline to the 26-week follow-up. The sample of 210 allows us to detect a standardized slope of 0.2. The actual standard deviation for the cigarette consumption change score is 7.1. The detectable slopes are 0.37 for RRVF, 0.20 for positive affect, and 1.07 for subjective reward.

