#### Data analysis

3.10.2

Prior to analyses, the data will be screened for entry errors and outliers, the extent and type of missing data will be assessed, and the most appropriate method for dealing with the missing data will be selected. For Aim 1, longitudinal cigarette counts (normalized as percent of baseline) will be analyzed using mixed models (Gaussian family) in the primary analysis. The model will include predictors of time (continuous or discrete), study phase (baseline, switch period, or follow-up), flavor group, candidate covariates, and predictors (e.g., e-cigarette use). It will be tested using the z-scores corresponding to the study phase by flavor group interaction terms with fruit-flavored as the reference. For an intent-to-treat (ITT) analyses, ITT will be defined as those randomized to a flavor group at day 6.

For Aim 2, measures are summary scores and difference scores and will be addressed using multiple regression methods. We will first test whether participants randomized to fruit versus tobacco or menthol-flavored e-cigarettes report greater subjective reward, greater increases in positive affect, and have a higher relative reinforcing value of e-cigarette flavoring using the t-score associated with the group difference. We will then test whether these effects predict fewer cigarettes smoked per day during the 6-week switching phase and at the 26-week follow-up.

Next, we will evaluate whether subjective reward, positive affect, and relative reinforcing value for entry into a model as predictors of change in cigarettes smoked per day (mean switch phase or follow-up cigarettes minus mean baseline cigarettes), using the significance of the corresponding t-score while controlling for craving, withdrawal, and negative affect relief. The series of regressions will occur within a structural equation model, with the effects of flavor (predictor) on cigarettes per day (outcome) across the switch follow-up phases mediated by subjective reward, positive affect, and the relative reinforcing value of flavor. We will compute the proportion of mediation for the indirect effects and evaluate the mediated paths for significance using the delta method and bootstrapped standard errors [[68], [69], [70]].

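### Week-26 smoking is measured by recall but compared with a filter-count baseline, so the size of week-26 change on the secondary endpoint mixes change in smoking with change of instrument

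*Protocol article*

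**What the plan says.** Three sections of the protocol article fix the instruments.

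- **Baseline, days 1-5 (3.4):** "Participants will collect all spent filters through day five". The dated bags are returned at the day 6 visit.
- **Switch phase, days 8-49 (3.8):** "Daily cigarette consumption will be determined by counting the daily spent cigarette filters returned for each of the 42 days".
- **Follow-up (3.8):** "Average CPD at the 26-week follow-up will be measured via a valid and reliable TLFB procedure". Section 3.1 describes this secondary endpoint as covering week 8 to week 26, again by TLFB.

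Section 3.10.2 then combines them. For Aim 1, "longitudinal cigarette counts (normalized as percent of baseline) will be analyzed using mixed models", and follow-up is the third level of the study-phase factor. For Aim 2 the outcome is the change in cigarettes per day, defined as "mean switch phase or follow-up cigarettes minus mean baseline cigarettes". Section 3.10.1 sizes Aim 2 for the same pair of changes: "from baseline to the end of the switch phase and from baseline to the 26-week follow-up".

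Table 1 lists baseline cigarettes per day for days 1-5 only. The article describes no TLFB at baseline or during the switch phase, and no check of agreement between the two methods. The CO threshold in 3.8 verifies abstinence; it does not check how many cigarettes were smoked.

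**The concern.** A filter count is physical, collected day by day and paid for. TLFB is recall, here over up to 19 weeks (weeks 8 to 26). Filters can go uncollected, and recall can be rounded or under-reported. The article calls TLFB valid and reliable, but that does not make it interchangeable with a filter count.

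As the analysis is written, the follow-up phase and the TLFB instrument coincide completely. A systematic gap between the methods therefore enters every baseline-to-week-26 change and every comparison of the switch phase with week 26, and nothing described in the article would allow it to be separated out.

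The trial's statements about later behavior rest partly on those quantities. Section 2 promises complete, partial and no switching as outcomes. Section 3.7 promises an account of whether early changes last, arrive late or reverse.

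**Working it through.** **1. The plan's own figure.** Section 3.10.1 gives a detectable difference of about 3.73 cigarettes per day (CPD) with 70 per group, 80% power and two-sided alpha 2.5%. The SD of the change score is given as 7.1.

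- Standard error: 7.1 × √(2/70) = 1.200.
- Normal approximation: 1.200 × (2.241 + 0.842) = 3.70.
- Noncentral t: 3.734.

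The figure reproduces. It is a difference between two arms.

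**2. Assumptions for the illustration.** None of these is in the article: TLFB reads r times the filter count, r from 0.8 to 1.2; baseline 10 to 20 CPD. The direction of any gap is unknown.

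**3. Within-person change.** A participant whose smoking has not changed shows an apparent change of (r − 1) × baseline.

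| Baseline (CPD) | r = 0.8 | r = 1.2 |
|---|---|---|
| 10 | −2 | +2 |
| 15 | −3 | +3 |
| 20 | −4 | +4 |

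On the percent-of-baseline scale the same participant reads 80% to 120%. With r = 0.8 an unchanged smoker looks like a partial switcher. With r = 1.2 a true fall to 83.3% of baseline reads as no change (0.833 × 1.2 = 1.0). Zero cigarettes stays zero under this model.

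**4. Arm contrast, gap common to all arms.**

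- *Additive offset c:* (Y₁ + c) − (Y₂ + c) = Y₁ − Y₂. It cancels.
- *Common ratio r:* the difference becomes r × (Y₁ − Y₂). A constant 3.73 CPD reads as 3.73 in the switch phase and as 0.8 × 3.73 = 2.98 to 1.2 × 3.73 = 4.48 at week 26. A steady benefit appears to shrink or grow by 20%. The SD of the week-26 percent-of-baseline values is multiplied by the same r, so the test at that time point barely moves, and a true difference of zero stays zero.

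**5. Arm contrast, gap differing by arm.** Allocation is unblinded (3.4). If recall differed by 10% between arms at a true mean of 5 to 10 CPD, a false difference of 0.5 to 1.0 CPD would appear. With standard error 1.200, the rejection rate under no true difference would be 3.8% to 8.1% instead of 2.5%. The article gives no evidence that recall differs by arm.

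**6. Aim 2 precision.** Person-to-person variation in r adds noise to the change score. Take an SD of 0.2 for r (the half-width of the assumed range) and 10 CPD at week 26. The added SD is 0.2 × 10 = 2.0, and √(7.1² + 2.0²) = √54.41 = 7.38, about 4% above 7.1. If the variation is unrelated to the mediators, it widens intervals without biasing slopes.

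**7. Sensitivity analyses (3.10.3).** Last observation carried forward and return to baseline can place a filter count beside other participants' TLFB values. Under return to baseline, the artefact in the arm contrast is (1 − r) × baseline × (difference in dropout proportion). Even if the arms differed by the whole anticipated 15%, with a 15 CPD baseline and r = 0.8 this is 0.2 × 15 × 0.15 = 0.45 CPD. With equal dropout it is zero.

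**The case against.** The case against making much of this is strong, and most of it stands.

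- **Primary endpoint.** Baseline to day 49 uses filter counts throughout, so it is untouched.
- **Complete switching.** It is verified by CO and does not rest on a subtraction across instruments.
- **Flavor hypotheses.** These are between-arm and are tested through the phase-by-flavor interaction. A common offset cancels there, and a common ratio preserves the null.
- **Size.** The ratio and the baseline values are assumed.
- **Silence.** The article is condensed, and a fuller protocol may include an earlier TLFB.
- **Remedy.** Recalling five or seven days while filters are being bagged is an easier task than recalling up to 19 unsupervised weeks.

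Two stronger readings are tempting. A reader might infer that the change of instrument creates a false flavor effect. That would need recall or filter return to differ by arm; the open-label design does not exclude this, but the documents do not show it. A reader might also set the ±3 CPD within-person shift beside 3.73 CPD and conclude that the artefact is nearly as large as the target effect. The first is a shift within a person and the second a difference between arms, so they are not comparable. Likewise, multiplying the arm difference by 0.8 to 1.2 while holding the SD at 7.1 would put power at about 60% to 93%, but the SD of the week-26 values scales too, so no such loss or gain should be claimed.

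The objection does not remove the explicit definition in 3.10.2. The article itself names both instruments, fixes baseline as days 1-5 and specifies follow-up minus baseline. If a baseline TLFB does exist, that definition still needs to say that it is the reference.

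**Conclusion.** The concern holds for the week-26 secondary endpoint and for the follow-up version of Aim 2, and not beyond them. As written, the analyses subtract or divide across two instruments, with no overlapping measurement described.

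The exposed results are the size of within-person change, the partial-switching and no-switching categories, and the comparison of the switch-phase effect with the week-26 effect. Under the assumed ratio of 0.8 to 1.2, an unchanged smoker reads 80% to 120% of baseline, and a constant arm difference appears to change by up to 20% in either direction. The loss of Aim 2 precision and the artefact in the sensitivity analyses are smaller under the same kind of assumption.

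This should be corrected because the correction is cheap and the article draws conclusions about sustained effects. It is not a threat to the primary result.

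**What to change.** 1. Administer the TLFB for days 1-5 at the day 6 visit and for days 43-49 at the day 49 visit, when filters are also counted.
2. Compute week-26 change, percent of baseline and partial-switching category against the TLFB baseline, in a separate week-26 analysis.
3. Compare week 26 with week 7 using TLFB at both. In the sensitivity analyses for week 26, carry forward or return to a TLFB value.
4. Report the agreement between filter counts and TLFB in the two overlap periods.
5. Keep filter counts for the primary baseline-to-day-49 analysis.

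The text changes fall in 3.8, 3.10.2 and 3.10.3. Participants already past day 6 can still supply the day 49 overlap.

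The cost is about ten minutes of participant time in total, a second baseline value, and a separate week-26 model in place of the single three-phase model. No visit is added. Calibration will be partial, because the overlap recall is short and aided by filter collection, and the report should say so.

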### Adverse event monitoring

3.9

Adverse events are monitored weekly during the switch phase using a self-report checklist. This checklist covers expected side effects of e-cigarette use and allows participants to list symptoms they are currently experiencing that are not on the list (unexpected). Adverse events are documented based on factors like severity, frequency, and type, and then reported to the PI, the Institutional Review Board, and the National Cancer Institute, in accordance with regulations.

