#### Flavor-associated subjective reward and positive affect (Day 6)

3.5.1

Participants will attend a laboratory session after overnight smoking abstinence (10 h; CO verified <10) on day 6 [23,34]. Cigarette craving, withdrawal symptoms, and positive and negative affect will be measured before e-cigarette exposure. They will receive instructions on how to use the e-cigarette before two e-cigarette exposures based on their flavor group assignment. On day 6, the traditional flavor groups will receive either two exposures of tobacco or two exposures of menthol flavoring, depending on their assignment. The fruit flavor group will receive blueberry and watermelon in a counterbalanced order. All exposures will have the same characteristics, only differing by flavor. Participants will take 14 puffs for the first exposure and 14 puffs for the second exposure. The exposures will be separated by 45 min [23,35]. After each exposure, participants will complete measures of subjective reward, craving, withdrawal, and affect. We chose to offer both watermelon and blueberry to participants randomized to fruit-flavored e-cigarettes to promote adherence if either flavor was unappealing. After this 1.25-h visit, participants will be compensated $40.

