The computer task will continue until a participant completes 10 trials and earns a total of 10 points, from which they will earn either one puff of an e-cigarette for each point (i.e., up to 10 puffs of an e-cigarette) or one puff of a cigarette for each point (i.e., up to 10 puffs of a cigarette). E-cigarette and/or cigarette puffs will be taken at the end of the procedure to prevent satiation from influencing responding in subsequent trials. RRVF is defined in relation to responding for cigarette puffs. The breakpoint is the highest trial that a participant is willing to work to earn a combustible cigarette puff and reflects the reinforcing value of cigarette smoking relative to e-cigarette vaping of the assigned flavor [23,37]. To ensure that responding is based on reinforcer preference rather than departure from the lab, the choice task will be followed by a 1-h wait in the laboratory. After completing this 2-h visit, participants will be compensated $45.

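### Adverse event monitoring is stated for the switch phase (from Day 8), but study product is first used on Days 6 and 7, and unlisted symptoms count only if current at the weekly check

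*Protocol article*

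**What the plan says.** Section 3.9 (Adverse event monitoring) sets the timing and the tool: "Adverse events are monitored weekly during the switch phase using a self-report checklist". It describes the form in two parts. For anticipated effects, "This checklist covers expected side effects of e-cigarette use". For anything else, the form "allows participants to list symptoms they are currently experiencing that are not on the list (unexpected"). On recording, "Adverse events are documented based on factors like severity, frequency, and type".

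The phase named in section 3.9 is dated by the heading of section 3.6.3: "Switch period (Weeks 2-7, days 8-49"). That section schedules visits on days 14, 21, 28, 35, 42 and 49.

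Study product is used before that phase. On Day 6 (section 3.5.1), after overnight abstinence, "Participants will take 14 puffs for the first exposure and 14 puffs for the second exposure". On Day 7 (section 3.5.2), the choice task yields 10 points in all, which can be worth "up to 10 puffs of an e-cigarette".

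For the analysis, section 3.10.2 states: "ITT will be defined as those randomized to a flavor group at day 6".

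**The concern.** An adverse event window normally opens no later than the first use of study product. Here the stated window opens at the switch phase, after both laboratory visits. Section 3.2 excludes people who vape on 5 or more days in 30, so participants are not regular vapers, and Day 6 is their first use of this product in the trial. The same section excludes allergy to propylene glycol or flavor additives, so the protocol itself foresees reactions to the product's components. First exposure is an obvious time to record them.

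A second point is the reference period for unlisted symptoms. A weekly form that asks only what is present now would not pick up an unexpected symptom that came and went during the week, and unexpected symptoms are what that item is for.

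At stake is how complete the safety data are around first exposure, and whether an early departure due to intolerance could be recognized as such. The primary outcome, the sample size and the error rates are not affected.

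**Working it through.** The plan gives no figure to reproduce. The check is a count of puffs, a comparison of dates and a reading of the form's wording.

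**Puffs before the stated window**

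- Day 6 (section 3.5.1): 14 + 14 = 28 puffs.
- Day 7 (section 3.5.2): 10 points are earned and split between e-cigarette and cigarette puffs by the participant's choices, so 0 to 10 e-cigarette puffs.
- Total before Day 8: 28 + 0 = 28 to 28 + 10 = 38 puffs.

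**Time from exposure to the first check**

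- Section 3.9 says weekly, without naming the occasion. Assume that the checklist is given at the weekly visits of section 3.6.3. The first is then Day 14.
- From the Day 6 exposures: 14 - 6 = 8 days. From the Day 7 puffs: 14 - 7 = 7 days.
- If the first check could instead fall anywhere in the first week of the phase (Days 8 to 14), the gap from Day 6 ranges from 8 - 6 = 2 days to 14 - 6 = 8 days. In every case it comes after both laboratory visits.

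**Who could be missed**

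- Everyone randomized is in the intent-to-treat set as of Day 6.
- Someone who reacts on Day 6 or 7 and does not return is in that set but never reaches a weekly check. The article states no other occasion for the checklist.
- The number of such people cannot be estimated. The planned attrition of about 15% of 240 covers the whole period to week 26 and is not broken down by cause or time.

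**Reference period, by type of symptom**

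| Symptom | Reference period in section 3.9 | Resolves between weekly checks |
|---|---|---|
| Listed (expected) | None stated; frequency is recorded, which is compatible with a look-back | Cannot be determined from the text |
| Unlisted (unexpected) | Current symptoms | No stated route onto the form |

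**The case against.** The strongest objection is that this is a condensed article. Section 3.9 is three sentences long. It does not say that monitoring happens at no other time, or that an event seen at a laboratory visit would go unrecorded. Capture windows and spontaneous reporting are often left to the full protocol, which is not shown. The laboratory visits are also staffed, with 45 minutes between the Day 6 exposures and a one-hour wait on Day 7, so a marked reaction would probably be noticed. This stands in part. A reader might infer that reactions on Days 6 and 7 are lost, or that participants who leave early have no adverse event record at all; the text does not support either. It supports only that no planned route is stated. But the article is not merely silent: it names a window and a reference period, and neither fits its own exposure schedule.

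Table 1 and the Day 6 and Day 7 descriptions mention no checklist, but this proves nothing. Table 1 has no adverse event row for any column, and the description of the weekly visits omits the checklist too.

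A reader might also conclude that transient symptoms in general are missed. That does not follow, because the limit to current symptoms applies only to unlisted ones.

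Finally, a reader might treat Days 6 and 7 as a clean comparison of tolerability between flavors. They are not. Day 7 use is self-chosen and may be mixed with cigarette puffs, the fruit arm gets two different flavors on Day 6 while the other arms get one flavor twice, and allocation is unblinded. Comparative tolerability is not a stated aim, and the article plans no comparison of adverse event rates by flavor.

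**Conclusion.** The point holds as a mismatch between the stated monitoring window and the exposure schedule, together with an incomplete reference period. As written, weekly monitoring belongs to days 8-49, while 28 to 38 puffs of study product are taken on Days 6 and 7. The window and the puff counts come straight from the text. The 8-day gap rests on the assumption that the checklist is given at the weekly visits. Unlisted symptoms that resolve between checks have no stated route onto the form; for listed ones the look-back is simply not given.

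This is a cheap improvement to safety data. It is not an error in the design or analysis of the efficacy outcomes. If the full protocol already collects events from first exposure, one corrected sentence in section 3.9 is enough.

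**What to change.** In section 3.9:

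1. State that adverse event collection starts at the first exposure to study product on Day 6.
2. Give the existing checklist at the end of the Day 6 visit and during the one-hour wait on Day 7, in addition to the weekly checks.
3. Use the time since the last assessment as the reference period for both listed and unlisted symptoms.
4. Summarize events from Day 6 onward by assigned flavor, descriptively.

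This adds two uses of an existing form at visits already scheduled. The downside is a few minutes per visit and more minor events to record. It changes data collection only; the exposures and the management of participants stay as they are.
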